### Statistical analysis

Statistical analysis will use intention to treat principles and per protocol analysis. A mixed model ANCOVA will be undertaken, adjusting for baseline values of the dependent variables to determine the difference between groups for primary and secondary outcomes. In addition, a responder analysis will be undertaken to determine clinical significance [65]. Participants who achieve an increase in VISA-G scores greater than the minimal detectable change score (10 points) [60] will be categorised as responders. The difference between the proportions of responders and non-responders in the four groups will then be analysed with risk ratios, risk differences and numbers needed to treat [53]. Participants randomised into the single exercise arm will be analysed separately. Where data is missing, baseline data will be carried forward.

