### Sample size and power analysis

The sample size required for this RCT is 100 participants (25 in each group) to detect a minimal clinically important difference of 10 points on the VISA-G outcome measure, assuming a standard deviation of 13 (Alpha of 0.05 and a power of 80 %) [44]. To account for potential drop-out, we will recruit 116 participants (29 per group).

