#### Secondary outcome measures

Secondary outcome measures will include five questionnaires to assess pain and dysfunction. The following questionnaires will be administered at baseline, 12-weeks and 52-weeks: Oxford Hip Score (OHS) [63], global rating of change questionnaire, Assessment of Quality of Life (AQoL), Hip dysfunction and Osteoarthritis Outcome Score (HOOS) [64] and the Lateral hip Pain Questionnaire (unpublished, University of Queensland, Australia).

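### Carrying baseline forward for every missing value biases the primary VISA-G comparison, in a direction that depends on dropout and average improvement, and discards data the planned mixed model could use

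*Protocol article*

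**What the plan says.** The Statistical analysis section of the protocol article names intention-to-treat and per-protocol analyses. Its model is this: "A mixed model ANCOVA will be undertaken, adjusting for baseline values of the dependent variables to determine the difference between groups". The section closes with the missing-data rule: "Where data is missing, baseline data will be carried forward". The rule is not limited by outcome, visit or reason for missingness, and it is not labelled a sensitivity analysis. The same section defines a responder as a participant whose VISA-G gain exceeds 10 points.

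The Sample size and power analysis section sets 25 per group "to detect a minimal clinically important difference of 10 points on the VISA-G outcome measure", "assuming a standard deviation of 13", with alpha 0.05 and 80% power. It then raises recruitment from 100 to 116 (29 per group) to cover dropout, and gives no rate by arm.

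Under Secondary outcome measures, the questionnaires are "administered at baseline, 12-weeks and 52-weeks: Oxford Hip Score (OHS) [63], global rating of change questionnaire" and three others. The Failure to improve section offers participants who have worsened at 12 weeks a move to both active interventions, and says that their results will be analysed and presented separately.

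**The concern.** A mixed model fitted to the observed visits can use a 12-week score when the 52-week score is missing. The carry-forward rule instead returns that participant to her baseline at 52 weeks, whatever she had gained by 12 weeks.

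Zero change is not a neutral value in this trial. Every arm receives education, postural advice and a physiotherapist-prescribed programme, and may continue usual pain medication (Interventions; Exercise therapy), so improvement in all arms is plausible. If it occurs, the rule pulls each arm's mean towards zero in proportion to that arm's dropout. Equal dropout then dilutes a real difference, and unequal dropout can create or distort one.

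The allowance from 100 to 116 treats dropouts as removed from the analysis. Under the rule they stay in it with zero change, so the allowance does not restore the effect size on which the power statement rests.

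A smaller point concerns the global rating of change. It is itself a change score (below 0 means worse, per Failure to improve), so it has no informative baseline to carry forward or to adjust for.

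**Working it through.** **Inputs from the protocol article.** True difference 10, SD 13, alpha 0.05 (taken as two-sided), 25 per group needed, 29 per group recruited, 2 x 2 factorial design. Implied dropout: 1 - 100/116 = 13.8%.

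**Assumed, because the protocol gives none of these.** Control mean change m0 of 0, 10 or 20 points; the dropout split between arms; baseline-outcome correlation 0.5; dropout unrelated to outcome within arm.

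**The plan's own figure.** n per group = 2 x (1.96 + 0.84)^2 x 13^2 / 10^2 = 26.5, so 27 rather than 25. That gap is a separate matter and nothing below depends on it.

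**Expected estimate under the rule.** With control dropout d0, active dropout d1 and true effect D, the estimated difference is

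(1 - d1)(m0 + D) - (1 - d0) m0.

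**1. Equal dropout, 13.8%.** The m0 terms cancel: 10 x 0.862 = 8.62 for a true 10, and 0 for no effect. Power comes from ANCOVA simulation at 29 per arm (20,000 runs per setting):

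| Control change | Baseline carried forward | Observed data |
|---|---|---|
| 0 | 83% | 86% |
| 10 | 76% | 86% |
| 20 | 63% | 86% |

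Type I error stays near 5% in all three settings.

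**2. Unequal dropout, 5% control and 23% active (average 14%).**
- No effect, m0 = 10: 0.77 x 10 - 0.95 x 10 = -1.8.
- No effect, m0 = 20: 0.77 x 20 - 0.95 x 20 = -3.6.
- True 10, m0 = 10: 0.77 x 20 - 0.95 x 10 = 5.9.
- True 10, m0 = 20: 0.77 x 30 - 0.95 x 20 = 4.1.
- m0 = 0: no effect stays at 0, and a true 10 becomes 0.77 x 10 = 7.7.

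For m0 of 10 to 20, simulated type I error is about 9 to 18% at 29 per arm and 14 to 34% at 58 per arm (a factorial margin). At m0 = 0 it is about 5%.

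**3. Imbalance reversed, 23% control and 5% active.**
- True 10, m0 = 10: 0.95 x 20 - 0.77 x 10 = 11.3.
- True 10, m0 = 20: 0.95 x 30 - 0.77 x 20 = 13.1.
- True 10, m0 = 0: 0.95 x 10 = 9.5.

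**4. Milder split, 6.9% control and 20.7% active.** No effect becomes -1.4 (m0 = 10) or -2.8 (m0 = 20). Type I error is 7.4% and 12.8% at 29 per arm, and 10.5% and 21.3% at 58 per arm. A true 10 becomes about 6.5 and 5.2; with the split reversed, 10.7 and 12.1.

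**Comparator.** ANCOVA on observed data returned about 10 (or 0) with type I error near 5% in every setting. Dropout was simulated as unrelated to outcome, the condition under which that analysis is unbiased.

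**The case against.** A reader might infer that the rule always shrinks the effect, or always inflates type I error. Neither follows. With equal dropout and no effect, type I error stays near 5%. With zero mean change there is no false difference even when dropout is unequal. With heavier control dropout and improving controls, the effect is overstated.

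A reader might also infer that the MHT arms will lose more participants. The protocol does not establish this. The Adverse events section foresees hormone-related events that could interrupt treatment, but calls complications unlikely. Stopping the cream is also not the same as a missing questionnaire under intention to treat. Unequal dropout is a plausible risk, not a stated fact.

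The larger figures rest on control improvements of one to two times the target difference and on a more than fourfold dropout ratio, both assumed. The sham programme is described as not loading the tendon therapeutically, so small control change is possible; in that case, with equal dropout, the power cost is 83% against 86%. The simulation also favours observed-data analysis. If participants who leave have gained little, zero change could be nearer the truth, and that setting was not run.

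These points limit the size of the problem but do not remove it. The 8.6 in place of 10 under equal dropout needs no assumption about control change, and the protocol offers nothing to show that the unfavourable settings are excluded. That the article names no sensitivity analysis is not part of the criticism, since an unseen analysis plan may hold one; the criticism is of the rule that is stated.

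For the global rating of change, 0 can be read as no change, so carrying 0 forward is workable though crude, and a constant baseline covariate simply drops out. That point is minor.

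**Conclusion.** The concern holds in a conditional form. As written, the rule overrides observed follow-up information and makes the primary estimate depend on dropout. At the implied 13.8%, split equally, a 10-point effect loses about 1.4 points. Pairwise power falls by about 3 to 23 percentage points, depending on how much controls improve, and type I error is not affected.

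Bias away from a true null needs both unequal dropout and non-zero average change. Under the assumed 5% and 23% with control improvement of 10 to 20 points, it is 1.8 to 3.6 points against the arm with more dropout. Because the reversed imbalance inflates a true 10 to about 11 to 13, the rule cannot be defended as reliably conservative. Only the 10 points, the SD of 13 and the overall dropout come from the document; the remaining inputs are assumptions.

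**What to change.** - **Primary analysis.** Use a likelihood-based mixed model on all observed 12- and 52-week values, with baseline as covariate and group-by-time terms, and no single imputation.
- **Cross-over.** State that 12-week data are used for everyone. State how the 52-week scores of participants who crossed over under Failure to improve enter the model, and reconcile this with the statement that their results are analysed separately.
- **Sensitivity.** Keep baseline carried forward as a sensitivity analysis, next to a delta-adjusted multiple imputation.
- **Responder analysis.** Missing may still count as non-response.
- **Global rating of change (minor).** Analyse it without a baseline covariate and without baseline imputation.

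The cost is revised analysis wording and some extra programming; no participants, visits or data are added. The downside is that the primary model relies on data being missing at random, which is why the sensitivity analyses are needed.

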## Discussion

This study will be the first randomised controlled trial to compare the effectiveness of MHT alone, and with the combination of exercise therapy, to treat pain and dysfunction associated with GTPS. This study has been pragmatically designed to ensure that interventions implemented in this study can be integrated into policy and clinical practice if found to be effective in the treatment of GTPS in post-menopausal women. It aims to minimise bias through methodological features of randomisation, blinding where possible, concealed allocation and intention to treat analysis.

There are risks with any study involving pharmacological interventions, however considerable efforts have been made to minimise these. A transdermal method of administrating hormones has been chosen as it combines an efficacious use of oestrogen replacement with the safest route of administration [66]. Additionally it is the gold standard for menopausal hormone replacement therapy, as it has a lower risk of venous thromboembolism than oral administration [67]; it is easily formulated and titrated; and has an additional safety benefit of avoiding the hepatic ‘first pass’ effect associated with oral administration, thus avoiding changes in clotting factors and sex hormone-binding globulin [68].

The validity of GTPS as a clinical entity has been determined using convergence of validity principles, previously described by George and Delitto [69], and diagnostic criteria based on by Fearon et al. [70]. The convergence of validity principles involves gathering evidence from multiple sources with differing methodologies to determine if the underlying constructs are of similar meaning. Three main principles have been selected for the current study: expert opinion; biological plausibility; and diagnostic tests/strategies for minimising false positive diagnoses.

The validity of GTPS as a clinical entity is supported by research on biological plausibility. Pathological features of gluteus medius and minimus tendinopathy have been likened to that of supraspinatus tendinopathy and subacromial bursitis of the shoulder [1, 71–73]. Anatomically, the gluteus medius tendons inserts onto the lateral and posterior-superior portion of the greater trochanter [74], and the gluteus minimus onto the anterior portion of the greater trochanter and acts as a femoral head stabiliser through hip joint range [75]. The positioning of these tendons is such that loss of the lateral stability mechanism (frontal plane femoropelvic alignment and medio-lateral stability in standing) from hip abductor weakness [76], can cause compression of these structures and reproduction of lateral hip pain. Similarly, pain reproduction with passive elongation of the involved tendons or active contraction of these same tendons is reported as a clinical feature of gluteal tendinopathy/GTPS [42]. Clinical tests used to assess for GTPS in the trial are likely to reveal symptoms associated with one or both of these mechanisms. Additionally, common subjective clinical findings such as difficulty lying on their side at night [77, 78] and pain with weight bearing activities [1, 78, 79] will be identified using the VISA-G questionnaire.

Due to the difficulties in diagnosing GTPS, there are aspects of our diagnostic criteria that are likely to improve diagnostic accuracy and minimise false positive diagnoses. Tendon experts recommend a battery of tests be used for clinical assessment and interpretation of hip abductor function [76]. This study will only include participants if they score <80 on the VISA-G questionnaire (a measure of pain and dysfunction associated with the condition) and have reproduction of lateral hip pain on a minimum of 3/5 diagnostic clinical tests.

Based on the convergence of this quantitative research, as well as the expertise of one of the authors (JC) who is a world-renowned tendon expert, with over 30 years of clinical experience in the area of tendon structure, function and dysfunction, the diagnostic criteria used to identify GTPS in this study have acceptable validity.

Development of the gluteal tendon rehabilitation program is based on expert opinion and guided by management strategies of other lower limb tendons. Commencing the program with gluteal isometrics is used as an initial pain relieving strategy [50] prior to loading with internal perturbations (toe taps and hip swing). All gluteal exercises are performed avoiding compression of the gluteal tendons (no hip adduction/crossing midline), since compression is thought to induce tendon pathology [80] by altering mechanotransduction and causing fibrocartilage formation [81]. Additionally, activities involving hip adduction including side-lying in bed [77, 78], and weight-bearing activities (stair climbing, rising from a chair) have been associated in lateral hip pain [1, 78, 79]. In this program, all exercises aim at loading the gluteal tendon occur on a single leg as double leg exercises allow compensation with the other leg [82] and inefficient tendon loading. Furthermore, this program focuses on rehabilitation of the kinetic chain - sequenced physiologic muscle activations that allow performance of an integrated biomechanical task [83]. This has been recommended to ensure complete restoration of lower leg muscle-tendon function [84]. The sham exercise program, although activating the same muscle groups as the intervention, clinically, these exercises are not aimed at strengthening muscle groups or loading the gluteal tendons.

Study results will be disseminated to the wider health network by journal publication, and reported back to participants via email. The findings of this study will help determine the effectiveness of menopausal hormone therapy and exercise therapy in post-menopausal women with GTPS. Additionally it will identify if an exercise program targeted at loading of the gluteal tendons in addition to kinetic chain strengthening is more superior to that of a low load lower limb sham exercise program. The results of this study aim to help guide medical and allied health practitioners to make an informed decision on the management of GTPS.

## Trial status

Ongoing.

## Abbreviations

AQoL, assessment of quality of life; Fe, iron; FSH; follicle stimulating hormone; GTPS, greater trochanteric pain syndrome; HbA1c, haemoglobin A1c; HDL, high density lipoprotein; HHS, harris hip score; HOOS, hip dysfunction and osteoarthritis outcome score; LDL, low density lipoprotein; LFT, liver function test; MHT, menopausal hormone therapy; ODI, oswestry disability index; OHS, oxford hip score; TFT, thyroid function tests; VISA-G; victorian institute of sport Australia – gluteal questionnaire
